## 4.18 Data Quality Control

To assure the quality of the data, data collectors and supervisors will be trained and a regular supervision and follow-up will be made by supervisors and the principal investigator. In addition, a regular check-up for completeness and consistency of the data will be made on daily basis. The questionnaire is translated into Amharic language and back-translated into English by translators who are blind to the original questionnaire. To make the questionnaire standard, reliability and validity test will be done for scale variables. Pilot test and Pre-test of the tool will be carried out in the area which has similar characteristics with the study population in Anlemo district will be done before two weeks of the actual data collection to ensure clarity, wordings, logical sequence and skip patterns of the questions. The pre-tested sample will be not included in the study and modification will be made.

For the qualitative study: Silent and comfortable places and convenient times will be selected and arranged to conduct, in-depth interview with religious leaders so as to allow maximum concentration. Study participants will also be made to give a true answer through explaining the purpose and importance of the study and assuring the confidentiality of data they are going to provide. To enhance inter-coder reliability, the coders each will independently apply the code book to a selected and rich transcript and review any differences in their coding, which will be discussed and resolved.

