**Antenatal care service utilization**

Antenatal care service utilization will be measured based on “at least one ANC attendance” (Women who have attended at least one ANC check-up during their current pregnancy) and “four or more ANC attendance” (Women who attended four or more ANC visits) during their current pregnancy as reported by the participant.

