**PART II: REPRODUCTIVE HISTORY OF RESPONDENT**

| **Sir. No.** | **Questions** | **Responses** | **Skip to** |
| --- | --- | --- | --- |
| **201** | How many months pregnant are you?  Record number of completed months |  |  |
| **202** | Is this your first pregnancy? |  |  |
| **203** | Number of pregnancies |  |  |
| **204** | What was your age at your first pregnancy? | 1. _________ Yrs  2. I don‘t remember |  |
| **205** | Number of children born alive | Female ______ male ______ |  |
| **206** | Number of still birth | Female ______ male ______ |  |
| **207** | Number of abortion |  |  |
| **208** | How many of them were delivered at home? | 1. Live birth number______  2. Still birth number ____ |  |
| **209** | How many of them were delivered in health institution? | 1. Live birth number______  2. Still birth number ____ |  |
| **210** | Have you experienced death of neonate (age less than seven days)? | 1. Yes  2. No  3. I don‘t remember |  |
| **211** | If yes to Q, 210 how many times? |  |  |
| **212** | If yes to Q 210, where was the neonate born? | 1. Home  2. Health institution  3. Other (specify) ___________ |  |
| **213** | How many times have you given birth to a child  in the past five years? |  |  |
| **214** | When was your last child born? | ___________/_________  Month year |  |
| **215** | Where does the last baby belong in your birth order? |  |  |

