**PART III MATERNAL HEALTH SERVICE UTILIZATION**

| **Sir. No.** | **Questions** | **Responses** | **Skip to** |
| --- | --- | --- | --- |
| 301 | Is your current pregnancy planned? | 1. Yes 2. No |  |
| 302 | What was your feeling when you recognized your last pregnancy | 1. Happiness  2. Sadness  3. Nothing  4. Other (specify)_________________ |  |
| 303 | Did you face any health problem in this pregnancy? |  |  |
| 304 | If yes to Q 303, what were they? (*Do not read the choices*) | 1. Vaginal bleeding  2. Sever head ache  3. Face/ hand swelling  4. Persistent vomiting  5. Hypertension  6. Fit  7. Other (specify)_______________ |  |
| 305 | Did you visit a health facility during in this pregnancy? | 1. Yes  2. No |  |
| 306 | If yes to Q305, reason for visit | 1. Pregnancy related health problem  2. Health problems not related to pregnancy  3. For antenatal care  4. Other (specify) -------------------------- |  |
| 307 | Did you receive any antenatal care in this pregnancy? | 1. Yes  2. No |  |
| 308 | If you did not attend antenatal care, can you tell me the reasons? (Multiple answer is possible)  **(Do not read the choice)** | 1.No or little Knowledge about ANC  2. No health problem encountered  3. Health institution is too far from my home  4. Expense to ANC is unaffordable.  5.long waiting time  6.Poor handling by health care providers  7. Lack of transportation  8. Lack of time to go to health institution  9. Other (specify)---------------------- |  |
| 309 | If yes to Q 308, at what gestational age did you start pregnancy check-up? | 1. One to three months  2. Four to six months  3. Seven to nine months  4. I don‘t remember |  |
| 310 | How many times did you go for pregnancy check-up? | 1.One time  2.Two times  3.Three times  4.More than three times  5.Don't remember |  |
| 311 | To which institution did you go for  Antenatal care service? | 1. Hospital 2. Health center  3. Health station  4. Other (specify) ________________ |  |
| 312 | Why did you prefer this institution? | 1. Close to my house  2. Competent health worker  3. Fair price  Other (specify) _________ |  |
| 313 | Was health education given during each visit? | 1. Yes, always  2. Yes, sometimes  3. Not at all  4. Don‘t remember |  |
| 314 | If yes to Q 313, were you informed about danger  signs related to pregnancy | 1.Yes  2. No  3. Don‘t remember |  |

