# Annex 2 Amharic Version

የመጠይቁ መለያ ቁጥር
ቀበሌ

የቤት ቁጥር

የጠያቂ ስምና ፊርማ

ክፍል አንድ፡- ማህበረ-ዲሞክራሲያዊ ምላሽ ሰጪ ባህሪያት

| **Sir. No.** | **ጥያቄዎች** | **ምላሾች** | **Skip to** |
| --- | --- | --- | --- |
| 101 | ሙሉ ዕድሜ ዓመት |  |  |
| 102 | ዘርህ የቱ ነው? | 1. 1.ሀዲያ2.ጉራጌ3.ከምባታ4.ስልጤ5.ሌላ ይግለጹ |  |
| 103 | ሃይማኖትህ ምንድን ነው? | 1. 1.ፕሮቴስታንት2.ኦርቶዶክስ3.ሙስሊም4.ካቶሊክ5.ሌላ ይግለጹ። |  |
| 104 | የገቢ ምንጭ | --------- |  |
| 105 | ወርሃዊ ገቢ | --------Birr |  |
| 106 | ከጤና ጣቢያ አማካኝ ርቀት | በሜትር ------------- |  |
| 107 | ከሆስፒታል አማካይ ርቀት | በሜትር ------------- |  |
|  | ለእናቶች ጤና አገልግሎት ከፍለዋል? | 1. 1.አዎ2.አይ |  |
| 108 | ያገኙት ከፍተኛ የትምህርት ደረጃ ስንት ነው? | 1. መሃይም 2. ማንበብና መጻፍ ብቻ (መደበኛ ትምህርት የለም) 3. ክፍል 1-4 4. 5-8. 5. 9-10 6. 11 - 12 ክፍል 7. ከ12ኛ ክፍል በላይ |  |
| 109 | ሥራህ ምንድን ነው? | 1. የቤት እመቤት 2. ገበሬ 3. የመንግስት ሰራተኛ 4. ነጋዴ 5. የቤት ሰራተኛ 6.ሌላ (ይግለጹ)) |  |
| 110 | የጋብቻ ሁኔታዎ ምን ያህል ነው? | 1. በጭራሽ አላገባም  2. ያገባ  3.የተፋታ  4.የተለየ  5.የሞተባት  6.ሌላ (ይግለጹ) |  |
| 111 | የባልሽ ዕድሜ ሙሉ ዓመታት |  |  |
| 112 | የባልሽ ስራ | 1. የመንግስት ሰራተኛ 2. ነጋዴ 3.ገበሬ 4.ሌላ (ይግለዥ) |  |
| 113 | የባልሽ የትምህርት ደረጃ | 1. መሃይም 2. ማንበብና መጻፍ ብቻ (መደበኛ ትምህርት የለም) 3. ክፍል 1-4 4. 5-8. 5. 9-10 6. 11 - 12 ክፍል 7. ከ12ኛ ክፍል በላይ |  |
| 114 | የቤተሰብ መጠን |  |  |

ክፍል II፡ reproductive ምላሽ ሰጪ ታሪክ

| **Sir. No.** | **ጥያቄዎች** | **ምላሾች** | **Skip to** |
| --- | --- | --- | --- |
| **201** | ስንት ወር ነፍሰ ጡር ነህ?የተጠናቀቁ ወራት ብዛት ይመዝግቡ |  |  |
| **202** | ይህ የመጀመሪያ እርግዝናዎ ነው? |  |  |
| **203** | የእርግዝና ብዛት |  |  |
| **204** | በመጀመሪያው እርግዝናዎ ዕድሜዎ ስንት ነበር? | 1. ________ ዓመቶች 2. **አላስታውስም** |  |
| **205** | በህይወት የተወለዱ ልጆች ቁጥር | ሴት____ ወንድ ______ |  |
| **206** | ገና የተወለዱ ሰዎች ቁጥር | ሴት____ ወንድ ______ |  |
| **207** | የፅንስ ማስወረድ ቁጥር |  |  |
| **208** | ከነሱ ውስጥ ስንቶቹ በቤት ውስጥ ተወለዱ? | 1. የቀጥታ የልደት ቁጥር ______  2. አሁንም የልደት ቁጥር ____ |  |
| **209** | ስንቶቹ በጤና ተቋም ተወለዱ? | 1. የቀጥታ የልደት ቁጥር ______  2. አሁንም የልደት ቁጥር ____ |  |
| **210** | የአራስ ሞት አጋጥሞዎታል (ዕድሜ ከሰባት ቀን በታች)? | 1. አዎ  2. No  3. አላስታውስም። |  |
| **211** | ለ Q 210 አዎ ከሆነ ስንት ጊዜ? |  |  |
| **212** | ለ Q 210 አዎ ከሆነ , አዲስ የተወለደው ሕፃን የት ነው የተወለደው? | 1. ቤት  2. የጤና ተቋም  3. ሌላ (ይግለጹ)___________ |  |
| **213** | ባለፉት አምስት ዓመታት ውስጥ ስንት ጊዜ ልጅ ወለዱ? |  |  |
| **214** | የመጨረሻ ልጅህ መቼ ነው የተወለደው? | ___________/_________  Month year |  |
| **215** | በትውልድ ቅደም ተከተልዎ ውስጥ የመጨረሻው ልጅ የት ነው ያለው? |  |  |

ክፍል III የእናቶች ጤና አገልግሎት አጠቃቀም

| **Sir. No.** | **ጥያቄዎች** | **ምላሾች** | **Skip to** |
| --- | --- | --- | --- |
| 301 | የአሁኑ እርግዝናዎ የታቀደ ነው? | 1. አዎ 2. አይደለም |  |
| 302 | የመጨረሻ እርግዝናዎን ሲያውቁ ምን ስሜት ነበር | 1. ደስታ 2. ሀዘን 3. ምንም 4. ሌላ (ይግለጹ)_____ |  |

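### The Amharic form does not plainly ask for stillbirths (Q206 and the sub-labels of Q208/Q209), so that listed variable may be invalid, and the Q310 code for four or more ANC visits is mislabelled

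*Protocol*

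**What the plan says.** The English questionnaire (Annex 1, Part II) takes the number of children born alive at Q205 and "Number of still birth" at Q206. Q208 and Q209 ask how many were delivered at home and in a health institution, each split into live births and "Still birth number". The second Section 4.7.1 (independent variables, reproductive history) lists stillbirth, home delivery and institutional delivery.

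In the Amharic form (Annex 2), Q205 is "በህይወት የተወለዱ ልጆች ቁጥር", a correct rendering of children born alive. Q206 is "ገና የተወለዱ ሰዎች ቁጥር".

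For antenatal care, the operational definitions give two measures: "Women who have attended at least one ANC check-up during their current pregnancy" and "Women who attended four or more ANC visits". In English, Q310 code 4 is "More than three times", and it is the only code that identifies the second measure.

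On translation, Section 4.18 says: "The questionnaire is translated into Amharic language and back-translated into English by translators who are blind to the original questionnaire". It also plans a pre-test of the tool two weeks before data collection, with modification afterwards.

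**The concern.** A listed variable should be collected by an item that asks for it. If the Amharic text is used as printed, a woman asked Q206 could report a recent birth, could report nothing, or could be asked whatever the interviewer takes the item to mean. The same form serves baseline and end line (title of Annex 1), and Section 4.17 places the end-line interview one month after delivery, when a question about people just born most readily suggests the new baby. A stillbirth history gathered under the wrong question cannot be reliably rebuilt from the data afterwards.

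The Q310 label matters for a different reason: it marks the cut that defines one of the two antenatal-care measures under Objective 2.

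The printed errors also bear on the quality control. Section 4.18 puts the blinded back-translation in the present tense, yet the annexed form still carries wording that a back-translation would be expected to expose.

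**Working it through.** No formula applies. The check sets the English and Amharic items side by side and then traces the variables they feed. The Amharic glosses below are my reading and need a native speaker's confirmation.

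- **Q205.** English: children born alive. Amharic: "በህይወት የተወለዱ ልጆች ቁጥር", the same meaning. A correct phrase for 'born alive' is therefore already on the form.
- **Q206.** English: "Number of still birth". Amharic: "ገና የተወለዱ ሰዎች ቁጥር", literally the number of people just or newly born. Nothing in it refers to death. It keeps the female and male blanks of the English item.
- **Q208 and Q209, stems.** The Amharic asks how many were born at home and how many in a health institution. Both match the English.
- **Q208 and Q209, sub-labels.** The English splits each answer into live births and "Still birth number". In Amharic the first label reads as 'direct birth number' and the second as 'even-now birth number', so 'still' has been taken as an adverb. These labels do not repair Q206.
- **Rest of Part II.** Q207 covers abortion and Q210 covers death of a baby under seven days old. Neither asks for stillbirths. It follows that no Amharic item in Part II asks for them plainly.
- **Where stillbirth is used.** Section 4.7.1 lists it as an independent variable. Section 4.19 names no covariate set: the effect models adjust for clustering, and for baseline differences through a period-by-allocation interaction. The determinants model also has no stated covariates. It is tied to birth preparedness in Section 4.19 and to skilled delivery in the Summary. Stillbirth could enter a determinants model, but nothing places it in the model for the intervention effect.
- **Q310.** In Amharic, codes 1 to 3 correctly read one, two and three times, code 4 reads 'more than threefold', and code 5 is 'don't remember'. The stem still asks how many times she went. A woman with four visits has no competing code, so four or more is code 4 against codes 1 to 3.
- **What Q310 code 4 feeds.** Only the four-or-more measure. The at-least-one measure can be taken from Q307, which asks directly whether any antenatal care was received.

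**The case against.** The best defence is that the form is not self-completed. Section 4.16 specifies face-to-face interviews by trained interviewers, Section 4.17 requires a health background, and baseline uses clinical nurses. Q206 directly follows a correct 'born alive' item and comes just before abortion, so an experienced interviewer may well see what is meant. Section 4.18 already provides for back-translation, a pre-test of wording and modification afterwards.

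Much of this stands. A reader might infer that the stillbirth variable simply becomes a count of births. That would require the item to be read out word for word and answered literally. It would also apply mainly at end line, because at baseline the women are less than 20 weeks pregnant and most would have no baby just born. The documents support 'ambiguous and possibly invalid', and no more.

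The defence does not remove the defect. Relying on interviewers to mend a question leaves the wording actually put to the woman unrecorded. The protocol describes translation into Amharic only and recruits Hadiyisa-speaking collectors, and the annexes hold no Hadiyisa questionnaire. If interviews are held in Hadiyisa, which is not stated, collectors would be translating a faulty Amharic source on the spot. Since Section 4.17 assigns collectors to different clusters, their repairs could differ by cluster. The planned pre-test is still ahead and is no reason to leave known errors in the form.

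One might also try to derive stillbirths as pregnancies minus live births, abortions and the current pregnancy. That fails with multiple births, with miscarriages not counted as abortions, and where it is unclear whether the current pregnancy was included in the total.

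**Conclusion.** The point holds as a wording error with a limited consequence. As printed, Amharic Q206 and the second sub-label of Q208 and Q209 do not ask for stillbirths as the English form does, so a listed independent variable is ambiguous and may be invalid in any determinants analysis that uses it. Q310 code 4 is mislabelled, but its position leaves its meaning largely recoverable.

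Three stronger readings are not supported:

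- **Bias in the intervention effect.** Section 4.19 does not name stillbirth as an adjustment variable, so no effect estimate is shown to depend on Q206.
- **Loss of the place-of-delivery history.** The stems of Q208 and Q209 are correct. Only the live/still split beneath them is garbled.
- **A measurable misclassification of antenatal care.** The documents give no basis for a miscoding rate, so none can be stated, and the at-least-one measure is untouched.

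The conclusion assumes that the annexed Amharic text is the text that will be used, and that a native speaker confirms the readings given here. The protocol does not show the wording loaded in the electronic form.

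**What to change.** Before the ODK form is locked:

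- Reword Amharic Q206 and the live/still sub-labels of Q208 and Q209, using the 'born alive' phrase already correct in Q205 and a matching 'born dead'.
- Write Q310 code 4 as 'four or more times'.
- Have a native Amharic speaker confirm the revised items.
- Repeat the Section 4.18 back-translation for these items and keep a record of it.
- Check that the wording loaded in ODK is the corrected wording.

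The cost is a few words in the Amharic form and the ODK file, plus a short repeat back-translation. The design, sample size and analysis do not change.

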**ክፍል VI የእርግዝና ስጋት ግንዛቤ**

1. በዚህ እርግዝና ወቅት ለራሴ ያለው አደጋ፡-

ምንም ስጋት የለም እጅግ በጣም ከፍተኛ ስጋት

1. በዚህ እርግዝና ወቅት የማኅፀን ልጅ ስጋት፡-

ምንም ስጋት የለም እጅግ በጣም ከፍተኛ ስጋት

1. በዚህ እርግዝና ወቅት የደም መፍሰስ ችግር (ብዙ ደም የማጣት) ስጋት፡-

ምንም ስጋት የለም እጅግ በጣም ከፍተኛ ስጋት

1. በቀዶ ሕክምና የመውለድ ዕድሌ፡-

ምንም ስጋት የለም እጅግ በጣም ከፍተኛ ስጋት

1. በዚህ እርግዝና ወቅት የመሞት ዕድሌ፡-

ምንም ስጋት የለም እጅግ በጣም ከፍተኛ ስጋት

1. ልጄ ያለጊዜው የመወለድ አደጋ፡-

ምንም ስጋት የለም እጅግ በጣም ከፍተኛ ስጋት

1. የልጄ የወሊድ ችግር ያለበት አደጋ፡-

ምንም ስጋት የለም እጅግ በጣም ከፍተኛ ስጋት

1. ልጄ ወደ አራስ ሕፃን ከፍተኛ እንክብካቤ ክፍል የመሄድ አደጋ የሚከተለው ነው፡-

ምንም ስጋት የለም እጅግ በጣም ከፍተኛ ስጋት

1. በዚህ እርግዝና ወቅት ልጄ የመሞት አደጋ፡-

እጅግ በጣም ከፍተኛ ስጋት እጅግ በጣም ከፍተኛ ስጋት

ክፍል VII ደህንነቱ የተጠበቀ የወሊድ አገልግሎት አጠቃቀም ላይ ያለ አመለካከት

| 701 | አንዳንድ ሰዎች ማንኛውም ነፍሰ ጡር ሴት የመውለድ ችግር ሊፈጠር ይችላል ብለው ያምናሉ | 1. በጣም አልስማማም, 2. አልስማማም, 3. ገለልተኛ, 4. እስማማለሁ, 5. በጣም እስማማለሁ |  |
| --- | --- | --- | --- |
| 702 | አንዳንድ ሰዎች የወሊድ ችግሮች ለሴት ጤንነት አደገኛ ሊሆኑ እንደሚችሉ ይሰማቸዋል | 1. በጣም አልስማማም, 2. አልስማማም, 3. ገለልተኛ, 4. እስማማለሁ, 5. በጣም እስማማለሁ |  |
| 703 | የወሊድ ችግሮች አዲስ ለተወለደ ሕፃን ጤና አደገኛ ሊሆኑ እንደማይችሉ ይታመናል | 1. በጣም አልስማማም, 2. አልስማማም, 3. ገለልተኛ, 4. እስማማለሁ, 5. በጣም እስማማለሁ |  |
| 706 | በአንዳንድ ሰዎች እምነት አንዲት ሴት ልጇን የምትወልድበትን ቦታ አስቀድመህ ማቀድ አለባት | 1. በጣም አልስማማም, 2. አልስማማም, 3. ገለልተኛ, 4. እስማማለሁ, 5. በጣም እስማማለሁ |  |
| 707 | አንዳንድ ሴቶች ወደሚወልዱበት ቦታ እንዴት እንደሚደርሱ አስቀድመው ማቀድ እንደሌለባቸው ይሰማቸዋል. | 1. በጣም አልስማማም, 2. አልስማማም, 3. ገለልተኛ, 4. እስማማለሁ, 5. በጣም እስማማለሁ |  |
| 708 | አንዳንድ ሴቶች እያንዳንዱ ነፍሰ ጡር ሴት የሰለጠነ የወሊድ እንክብካቤ እንደሚያስፈልገው ይሰማቸዋል | 1. በጣም አልስማማም, 2. አልስማማም, 3. ገለልተኛ, 4. እስማማለሁ, 5. በጣም እስማማለሁ |  |
| 709 | ጥቂት ሴቶች በወሊድ ጊዜ የወንድ ጤና ባለሙያዎች መገኘት ሥነ ምግባር የጎደለው እና አሳፋሪ እንደሆነ ይሰማቸዋል | 1. በጣም አልስማማም, 2. አልስማማም, 3. ገለልተኛ, 4. እስማማለሁ, 5. በጣም እስማማለሁ |  |
| 710 | እንደ አንዳንድ ነፍሰ ጡር እናቶች ስሜት በወሊድ ክፍል ውስጥ አልጋ ላይ መውለድ በጣም አሳፋሪ ነው. | 1. በጣም አልስማማም, 2. አልስማማም, 3. ገለልተኛ, 4. እስማማለሁ, 5. በጣም እስማማለሁ |  |
| 711 | ብዙ ሴቶች ሴቶች ለመውለድ ወደ ጤና ተቋም አይሄዱም ብለው ያምናሉ፣ ይህም በዋነኝነት በጣም ውድ ስለሆነ ነው። | 1. በጣም አልስማማም, 2. አልስማማም, 3. ገለልተኛ, 4. እስማማለሁ, 5. በጣም እስማማለሁ |  |
| 712 | ብዙ ሴቶች ሴቶች ለመውለድ ወደ ጤና ተቋም የማይሄዱት የጤና ባለሙያዎች በአክብሮት ስለማያዩአቸው እንደሆነ ያምናሉ  . | 1. በጣም አልስማማም, 2. አልስማማም, 3. ገለልተኛ, 4. እስማማለሁ, 5. በጣም እስማማለሁ |  |

ክፍል VIII የሃይማኖት መሪዎች የተሳትፎ ልኬት መለኪያ መሣሪያ

| 801 | በቀጠሮ ወይም በቀጠሮ ላይ ተመስርቼ የቅድመ ወሊድ ክትትል እንዳደርግ የሃይማኖት መሪዬ የማያቋርጥ ማሳሰቢያ ነበር። | 1. በጣም አልስማማም, 2. አልስማማም, 3. ገለልተኛ, 4. እስማማለሁ, 5. በጣም እስማማለሁ |  |
| --- | --- | --- | --- |
| 802 | የሀይማኖት መሪዎቼ ብረት ፎሌት ያለማቋረጥ መውሰድ እንዲጨርሱ ደጋግመው ያሳስባሉ | 1. በጣም አልስማማም, 2. አልስማማም, 3. ገለልተኛ, 4. እስማማለሁ, 5. በጣም እስማማለሁ |  |
| 803 | የሃይማኖት መሪዎቼ ስለ ቴታነስ ቶክሳይድ ክትባት ደጋግመው አሳውቀውናል። | 1. በጣም አልስማማም, 2. አልስማማም, 3. ገለልተኛ, 4. እስማማለሁ, 5. በጣም እስማማለሁ |  |
| 804 | የሃይማኖት መሪዎቼ ስለ ግብረ ሥጋ ግንኙነት የሚተላለፉ በሽታዎች እና ስለ ኤችአይቪ ምርመራ እና ምክር ደጋግመው አሳውቀውናል። | 1. በጣም አልስማማም, 2. አልስማማም, 3. ገለልተኛ, 4. እስማማለሁ, 5. በጣም እስማማለሁ |  |
| 805 | የሃይማኖት መሪዎቼ የሰለጠነ የወሊድ አገልግሎትን እንድንለይ ገፋፍተውናል። | 1. በጣም አልስማማም, 2. አልስማማም, 3. ገለልተኛ, 4. እስማማለሁ, 5. በጣም እስማማለሁ |  |
| 806 | የሃይማኖት መሪዎቼ በጤና ተቋም እንድንወልድ ያበረታቱናል። | 1. በጣም አልስማማም, 2. አልስማማም, 3. ገለልተኛ, 4. እስማማለሁ, 5. በጣም እስማማለሁ |  |
| 807 | የሃይማኖት መሪዎቼ በምጥ ጊዜ መጓጓዣ እንድናዘጋጅ ያበረታቱናል። | 1. በጣም አልስማማም, 2. አልስማማም, 3. ገለልተኛ, 4. እስማማለሁ, 5. በጣም እስማማለሁ |  |
| 808 | የሃይማኖት መሪዎቼ በወሊድ ጊዜ እና በድህረ ወሊድ ወቅት ለእኔ እና ለቤተሰቤ የድጋፍ ምንጮችን እንድንለይ በተለምዶ ያበረታቱናል። | 1. በጣም አልስማማም, 2. አልስማማም, 3. ገለልተኛ, 4. እስማማለሁ, 5. በጣም እስማማለሁ |  |
| 809 | የሃይማኖት መሪዎቼ ከወሊድ ጋር የተያያዙ ተጨማሪ ወጪዎችን እንድናዘጋጅ፣ ለእኔ እንክብካቤ እና አዲስ ለተወለደው ልጄ እንክብካቤ የሚያስፈልጉትን ነገሮች እንድናዘጋጅ በተለምዶ ያበረታቱናል። | 1. በጣም አልስማማም, 2. አልስማማም, 3. ገለልተኛ, 4. እስማማለሁ, 5. በጣም እስማማለሁ |  |
| 810 | የሃይማኖት መሪዎቼ በእርግዝና ወቅት ስለ አደገኛ ምልክቶች ደጋግመው አሳውቀውናል። | 1. በጣም አልስማማም, 2. አልስማማም, 3. ገለልተኛ, 4. እስማማለሁ, 5. በጣም እስማማለሁ |  |
| 811 | የሃይማኖት መሪዎቼ በምጥ እና ልጅ በሚወልዱበት ወቅት ስለ አደገኛ ምልክቶች ደጋግመው አሳውቀውናል። | 1. በጣም አልስማማም, 2. አልስማማም, 3. ገለልተኛ, 4. እስማማለሁ, 5. በጣም እስማማለሁ |  |
| 812 | የሃይማኖት መሪዎቼ ከወሊድ በኋላ ባሉት ጊዜያት ስለ አደገኛ ምልክቶች ደጋግመው አሳውቀውናል። | 1. በጣም አልስማማም, 2. አልስማማም, 3. ገለልተኛ, 4. እስማማለሁ, 5. በጣም እስማማለሁ |  |
| 813 | የሃይማኖት መሪዎቼ አዲስ ስለተወለዱ የአደጋ ምልክቶች ደጋግመው አሳውቀውናል። | 1. በጣም አልስማማም, 2. አልስማማም, 3. ገለልተኛ, 4. እስማማለሁ, 5. በጣም እስማማለሁ |  |
| 814 | የሃይማኖት መሪዎቼ በእርግዝና ወቅት፣ ምጥ እና ልጅ በሚወልዱበት ወቅት፣ እና አዲስ በተወለደ፣ ከወሊድ በኋላ በሚከሰት ጊዜ ማንኛውም የአደጋ ምልክቶች ሲከሰቱ ጤናን ቀድመን እንድንፈልግ አስታውሰውናል። | 1. በጣም አልስማማም, 2. አልስማማም, 3. ገለልተኛ, 4. እስማማለሁ, 5. በጣም እስማማለሁ |  |
| 815 | የሀይማኖት መሪዎቼ የድህረ ወሊድ አገልግሎት እንድንከተል ያበረታቱናል። | 1. በጣም አልስማማም, 2. አልስማማም, 3. ገለልተኛ, 4. እስማማለሁ, 5. በጣም እስማማለሁ |  |
| 816 | የኃይማኖት መሪዎቼ ስለ ቤተሰብ ምጣኔ እና ስለ ሕፃን ክትባቶች በተለምዶ ያሳውቁን ነበር። | 1. በጣም አልስማማም, 2. አልስማማም, 3. ገለልተኛ, 4. እስማማለሁ, 5. በጣም እስማማለሁ |  |
| 817 | የሃይማኖት መሪዎቼ አዲስ ስለተወለደው እንክብካቤ ብዙ ጊዜ ያሳውቁን ነበር። | 1. በጣም አልስማማም, 2. አልስማማም, 3. ገለልተኛ, 4. እስማማለሁ, 5. በጣም እስማማለሁ |  |
| **818** | የሀይማኖት መሪዎቼ የእናቶች እና የህፃናት ጤና መልእክቶችን በጉባኤው ላይ ያሰራጫሉ። | 1. በጣም አልስማማም, 2. አልስማማም, 3. ገለልተኛ, 4. እስማማለሁ, 5. በጣም እስማማለሁ |  |
| **819** | የሃይማኖት አባቶች ለእናቶች እና ህጻናት ጤና እድገት ጠቃሚ የሆነ ድጋፍ ይሰጣሉ | 1. በጣም አልስማማም, 2. አልስማማም, 3. ገለልተኛ, 4. እስማማለሁ, 5. በጣም እስማማለሁ |  |
| **820** | በእርግዝና እና ልጅ በምወለድበት ጊዜ የሃይማኖት መሪዎች እንደረዱኝ ይሰማኛል | 1. በጣም አልስማማም, 2. አልስማማም, 3. ገለልተኛ, 4. እስማማለሁ, 5. በጣም እስማማለሁ |  |
| **821** | በእርግዝና እና በወሊድ ጊዜ የእናቶች እና የህፃናት ጤና አጠባበቅ እንድገኝ በማበረታታት የሃይማኖት መሪዎች እንደረዱኝ ይሰማኛል። | 1. በጣም አልስማማም, 2. አልስማማም, 3. ገለልተኛ, 4. እስማማለሁ, 5. በጣም እስማማለሁ |  |
| **822** | የአደጋ ምልክቶች በሚታዩበት ጊዜ ሁሉ የጤና እንክብካቤ ለመፈለግ ሲነሱ የሃይማኖት መሪዎች ድጋፍ እንደሚሰጡኝ ይሰማኛል። | 1. በጣም አልስማማም, 2. አልስማማም, 3. ገለልተኛ, 4. እስማማለሁ, 5. በጣም እስማማለሁ |  |
| **823** | የእናቶች እና ህፃናት ጤናን በተመለከተ ከሀይማኖት አባቶች ድጋፍ እንደተደረገልኝ ይሰማኛል። | 1. በጣም አልስማማም, 2. አልስማማም, 3. ገለልተኛ, 4. እስማማለሁ, 5. በጣም እስማማለሁ |  |
| **824** | የሃይማኖት መሪዎች ስለ እናቶች እና ህፃናት ጤና ጠንቅቀው ያውቃሉ ብዬ አምናለሁ። | 1. በጣም አልስማማም, 2. አልስማማም, 3. ገለልተኛ, 4. እስማማለሁ, 5. በጣም እስማማለሁ |  |
| **825** | የሃይማኖት መሪዎች የእናቶች እና የህፃናት ጤና መልዕክቶችን ሲያስተላልፉ ነፍሰ ጡር እናቶች እንደሚቀበሏቸው ተረድቻለሁ | 1. በጣም አልስማማም, 2. አልስማማም, 3. ገለልተኛ, 4. እስማማለሁ, 5. በጣም እስማማለሁ |  |
| **826** | የሃይማኖት መሪዎች ለእናቶች እና ህጻናት ጤና እድገት ታማኝ አስተዋፅዖ አበርክተዋል ብዬ አምናለሁ። | 1. በጣም አልስማማም, 2. አልስማማም, 3. ገለልተኛ, 4. እስማማለሁ, 5. በጣም እስማማለሁ |  |
| **827** | የሃይማኖት መሪዎች ስለ እናቶች እና ህፃናት ጤና ሲያስተምሩ እና ሲሰጡ ይታመናሉ ብዬ አምናለሁ። | 1. በጣም አልስማማም, 2. አልስማማም, 3. ገለልተኛ, 4. እስማማለሁ, 5. በጣም እስማማለሁ |  |
| **828** | የእናቶች ጤና አገልግሎት በአግባቡ ጥቅም ላይ መዋሉን እና አለመሆኑን የሀይማኖት መሪዎች እየተከታተሉት እንደሆነ እገነዘባለሁ። | 1. በጣም አልስማማም, 2. አልስማማም, 3. ገለልተኛ, 4. እስማማለሁ, 5. በጣም እስማማለሁ |  |
| **829** | የሃይማኖት መሪዎች ስለ መደበኛ የእናቶች እና ህጻናት ጤና አገልግሎት አጠቃቀምን የመከታተል ሃላፊነት እንደሚወስዱ ተረድቻለሁ | 1. በጣም አልስማማም, 2. አልስማማም, 3. ገለልተኛ, 4. እስማማለሁ, 5. በጣም እስማማለሁ |  |
| **830** | የሃይማኖት መሪዎች በታዘዘው መሠረት የብረት-ፎሌት መድኃኒቶችን የመቆጣጠር ኃላፊነት እንዳለባቸው እንደሚሰማቸው ተገንዝቤያለሁ | 1. በጣም አልስማማም, 2. አልስማማም, 3. ገለልተኛ, 4. እስማማለሁ, 5. በጣም እስማማለሁ |  |
| **831** | የሀይማኖት መሪዬ የእናቶች እና የህፃናት ጤና መልእክቶችን ሲያሰራጭ በመመልከቴ ተደንቄያለሁ እና ተጽኖአለሁ። | 1. በጣም አልስማማም, 2. አልስማማም, 3. ገለልተኛ, 4. እስማማለሁ, 5. በጣም እስማማለሁ |  |
| **832** | ከሀይማኖት መሪዎቼ ቤተሰብ ያየሁትን በመከተል የእናቶች እና የህፃናት ጤና አጠባበቅ አገልግሎቶችን በመደበኛነት እንደማገኝ እርግጠኛ ነኝ | 1. በጣም አልስማማም, 2. አልስማማም, 3. ገለልተኛ, 4. እስማማለሁ, 5. በጣም እስማማለሁ |  |
| **833** | የሃይማኖት መሪዎች በህመም ጊዜ እንክብካቤን በመፈለግ ረገድ አርአያ ሊሆኑ እንደሚችሉ ይሰማኛል። | 1. በጣም አልስማማም, 2. አልስማማም, 3. ገለልተኛ, 4. እስማማለሁ, 5. በጣም እስማማለሁ |  |
| **834** | የእናቶችና ህጻናት ጤና መልእክቶችን ሲያሰራጩ የሃይማኖት አባቶች ተስተውለዋል። | 1. በጣም አልስማማም, 2. አልስማማም, 3. ገለልተኛ, 4. እስማማለሁ, 5. በጣም እስማማለሁ |  |
| **835** | በቤተ ክርስቲያናችን/መስጊድ የሀይማኖት አባቶች የእናቶችንና የህፃናትን ጤና በማስተዋወቅ ረገድ ባብዛኛው ይስተዋላል | 1. በጣም አልስማማም, 2. አልስማማም, 3. ገለልተኛ, 4. እስማማለሁ, 5. በጣም እስማማለሁ |  |
| **836** | የሃይማኖት አባቶች ከእርግዝና፣ ምጥ እና ልጅ መውለድ ጋር የተያያዙ ጎጂ ልማዳዊ ድርጊቶችን እንደሚያበረታቱ በመግለጽ ይስተዋላል | 1. በጣም አልስማማም, 2. አልስማማም, 3. ገለልተኛ, 4. እስማማለሁ, 5. በጣም እስማማለሁ |  |

# Annex 2 Interview guide for qualitative study

**The role of religious leaders in promoting maternal and child health: a qualitative exploration of religious leaders’ perspective/view in rural setting of Hadiya Zone, Southern Ethiopia.**

**Interview guide**

1. Introductory questions
2. How many people are in your congregation?
3. How long have you had your position here?
4. Where were you previously appointed?
5. Do you have an idea of what the maternal health service utilizations coverage in your congregation is?
6. Do you receive questions about maternal health (ANC, SDS and PNC) from the members of your congregation?
7. What kinds of questions?
   - Interpretation of the bible and other text
   - Personal advice with regard to decision-making
   - Unhealthy beliefs and practices about maternal health service utilizations (ANC, SDS and PNC)
   - Unhealthy beliefs and practices about feeding new-borns
8. From whom and when?
9. How do you handle such?
10. Other questions?
11. Do you have an idea of the decision-making process regarding maternal health service utilizations in the families in your congregation? What factors are, in your opinion, decisive?
12. Do you, yourself, raise the topic of maternal health (ANC, SKD and PNC) for discussion?
13. During home visits?
14. During confirmation classes?
15. In sermons?
16. Otherwise
17. During congregation or on spiritual conference
18. Do you have contact with other religious leaders on the topic of maternal health or other topics?
19. From your own denomination?
20. From other denominations?
21. Regularly? Or only during spiritual conference?
22. Have you had contact with the government about maternal health (ANC, SDS and PNC) or other topics?
23. With the Kebele leaders or Head of Health office?
24. With the Health extension workers?
25. Regularly? Or only during spiritual conference?
26. What is your position on possibly obligatory maternal health (ANC, SDS and PNC)?
27. Is there anything else that you think is of importance and would therefore like to add?

